### Design

This study will be a single-center, equally randomized, two-armed, parallel, stratified (gender), subject-assessor-blinded, sham-controlled pilot trial. This trial is being conducted at the Pain and Spine Center, Dunsan Korean Medicine Hospital of Daejeon University (DKMHDU), Korea.

A total of 50 participants diagnosed with CNP will be recruited from the Clinical Trial Center of DKMHDU in Daejeon through advertisements in local newspapers, on hospital websites and bulletin boards, in information leaflets, etc. The recruitment period will run from May 2017 to December 2017. Clinical research coordinators will interview all potential participants over the telephone and schedule screening visits. At the screening visits, all potential participants will be informed of the objectives and the overall procedure of the trial and will be asked to provide written informed consent. Study volunteers will go through a screening process, which will include radiography of the cervical spine and physical examinations, to verify the diagnosis of non-specific CNP.

At visit 1, an eligible participant will receive baseline assessments, including the use of the acupuncture expectancy scale [30, 31], and will then be randomly allocated into one of two groups: the real TEA group and the sham TEA group. The real TEA group will receive TEA treatment at local acupoints in the neck region. The sham TEA group will receive the same treatment as the real TEA group, but with a sham device with the thread removed. Both groups will receive treatment once a week for a total of four sessions. The real TEA and the sham TEA will be described to the participants as “classical TEA” and “non-classical TEA,” respectively. Researchers will explain to the participants that the term “classical TEA” is “typically used in Korean Medicine clinics” while the term “non-classical TEA” is “rarely used in Korean Medicine clinics” [32, 33]. Outcome measures will be assessed before the treatment (week 1), 2 weeks after the first treatment (week 4), and 2 weeks (week 6) and 4 weeks (week 8) after the last treatment. A flowchart of the study is illustrated in Fig. 1, and the clinical trial schedule is presented in Fig. 2.

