### Participants

#### Inclusion criteria

A participant will be enrolled if they fulfill the following criteria: (1) age 19–65 years; (2) suffering from persistent or recurrent neck pain lasting longer than 3 months [34] (neck pain is defined as “pain, ache, or discomfort” in the area between the occiput and the third thoracic vertebra and between the medial borders of the scapulae [35]); (3) indicating pain of more than 40 mm on the visual analog scale (VAS) at the time of screening; (4) diagnosis of non-specific neck pain by a clinician based on history taking, physical examination, image examination, and medical examination; (5) able and willing to comply with the intervention and follow-up evaluation; and (6) able to provide written informed consent.

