### Statistical methods

#### Sample size

This pilot RCT is designed as a preliminary to a full-scale confirmatory trial. Therefore, we assume that a total of 50 participants will be an acceptable sample size, considering 20 participants in each group with a 20% drop-out rate.

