#### Statistical analysis

Data will be analyzed by an independent statistician who is blinded to the group allocation and who will use the Statistical Package for the Social Sciences (SPSS) Version 23.0 (IBM Inc., New York, NY, USA). The analysis set will consist of the Intent-to-treat (ITT) set, Per-protocol (PP) set, and Full Analysis Set (FAS). The ITT set will include all participants as originally allocated after randomization. The PP set will include the participants who completed three or more treatment sessions (75%) and the entire trial without any major violation of the protocol. Participants who are assessed at least once after random allocation will compose the FAS, which will be used for the main analysis of the treatment outcomes. Safety will be analyzed using the ITT set. The significance level will be set at *p* < 0.05. Missing data will be handled using the last-observation-carried-forward (LOCF) method.

The demographic and baseline characteristics, such as age, gender, medical history, duration of CNP and treatment expectancy, will be summarized for each treatment group. Depending on whether a normal distribution is found or not, baseline assessments for homogeneity will be conducted using the Wilcoxon rank sum test or the *t* test for continuous variables and Fisher’s exact test or the chi-square test for categorical variables.

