The primary outcome, the mean changes from baseline to week 6 in the VAS scores, will be compared between the two groups by using the *t* test or analysis of covariance (ANCOVA). If the baseline difference in the VAS score between the two groups is statistically significant, an ANCOVA will be performed with the baseline VAS score as a covariate and the study group as a fixed factor. The paired *t* test or the Wilcoxon signed rank test will be conducted to compare the treatment outcomes before and after intervention in each group. In addition, a repeated-measures analysis of variance (ANOVA) will be used to further confirm the differences in the trends of the visit. The secondary efficacy outcomes will be evaluated using the Wilcoxon rank sum test or the *t* test for continuous variables and Fisher’s exact test or the chi-square test for categorical variables. For safety assessments, all adverse events will be recorded as frequencies with percentages and durations. The chi-square test or Fisher’s exact test will be used to evaluate the statistical significance of between-group differences in the frequencies of adverse events. The duration of each adverse event will be compared between the two groups by using the Wilcoxon rank sum test or the *t* test. Subgroup analyses based on baseline characteristics will also be performed for the primary and the secondary outcomes.

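### Acupuncture expectancy is measured before randomisation, but the primary VAS comparison never adjusts for it: a cheap gain in precision is passed over, though the planned test remains valid

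*Protocol article*

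**What the plan says.** The Design section fixes the order of events on the day of allocation: "an eligible participant will receive baseline assessments, including the use of the acupuncture expectancy scale [30, 31], and will then be randomly allocated". Expectancy is therefore a true pre-randomisation value. The same section describes the trial as "single-center, equally randomized, two-armed, parallel, stratified (gender), subject-assessor-blinded, sham-controlled pilot trial", so gender is the only stratification factor and expectancy is not balanced by design.

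Statistical analysis gives expectancy two definite uses and one possible use. It is among the characteristics "such as age, gender, medical history, duration of CNP and treatment expectancy, will be summarized for each treatment group". The next sentence tests baseline assessments for homogeneity between the groups. The section ends with subgroup analyses on baseline characteristics, which are not named and could include expectancy.

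The primary outcome, change in the 100-mm VAS from baseline to week 6, is compared by a t test or ANCOVA. Only if the baseline VAS difference is significant, "an ANCOVA will be performed with the baseline VAS score as a covariate and the study group as a fixed factor". Neither version contains expectancy.

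**The concern.** The primary outcome is pain that participants rate themselves, in a sham-controlled acupuncture trial. Expectancy is a plausible predictor of such a score, and the authors chose to measure it. In the Discussion they also expect the sham needling itself to relieve pain, so the contrast between arms is the added effect of the thread alone, and a shift of a few millimetres could matter.

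The uses that the plan does make of expectancy do not touch the primary estimate. A homogeneity test has no stated consequence for expectancy, because the switch to ANCOVA depends on VAS alone. If the arms differed on expectancy, any adjustment would be decided after seeing the data. A subgroup analysis does not adjust the overall comparison. What is at stake is precision, and the error rate in those trials where the arms happen to differ on expectancy. Both bear on an estimate that is meant to inform a full-scale trial.

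**Working it through.** **Inputs from the article.** 20 evaluable per arm, 20% drop-out, 50 in total (Sample size); equal allocation, stratified by gender only (Design); "The significance level will be set at *p* < 0.05", taken here as two-sided (Statistical analysis).

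**Inputs assumed, because the article gives none.** VAS SD 20 mm; expectancy slope b = 0.2 to 0.4 outcome SD per expectancy SD; correlation rho = 0.4 to 0.6 between baseline and week-6 VAS; expectancy unrelated to baseline VAS.

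**1. The plan's own figure.** 20 / (1 − 0.20) = 25 per arm, 50 in total. It reproduces. There is no stated power, effect size or SD to reproduce.

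**2. How large a chance imbalance is.** The SD of the standardised difference in expectancy between arms is sqrt(2/n).
- n = 25: sqrt(2/25) = 0.283; probability of an imbalance above 0.5 SD is 7.7%.
- n = 20: sqrt(2/20) = 0.316; probability 11.4%.

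**3. Whether the homogeneity test would notice.** At 25 per arm an observed difference must exceed about 2.01 × 0.283 = 0.57 SD to reach p < 0.05. A difference of 0.5 SD (p about 0.08) passes as homogeneous.

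**4. Shift in the unadjusted estimate at 25 per arm.** Shift = imbalance × b × SD. For a 1-SD chance imbalance:
- b = 0.2: 0.283 × 0.2 × 20 = 1.1 mm
- b = 0.4: 0.283 × 0.4 × 20 = 2.3 mm

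For scale, with SD 20 mm the standard error of the difference is about 20 × 0.283 = 5.7 mm.

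**5. Overall and conditional type I error.** Null simulation, 40,000 trials, 20 per arm, r = correlation of expectancy with outcome:

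| | r = 0.3 | r = 0.5 |
|---|---|---|
| Unadjusted, all trials | 5.1% | 4.8% |
| Unadjusted, imbalance above 0.5 SD | 8.2% | 12.9% |
| Adjusted, imbalance above 0.5 SD | 4.7% | 4.3% |

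**6. Variance against ANCOVA on baseline VAS alone.** If expectancy adds b² to the variance left after baseline VAS, the ratio is (1 − rho²) / (1 − rho² + b²), times a small-sample penalty of about 1 + 1/(N − 5) for the extra covariate. With N = 50 the penalty is 1 + 1/45 = 1.022.
- rho = 0.4, b = 0.2: 0.84 / 0.88 × 1.022 = 0.98
- rho = 0.4, b = 0.4: 0.84 / 1.00 × 1.022 = 0.86
- rho = 0.6, b = 0.2: 0.64 / 0.68 × 1.022 = 0.96
- rho = 0.6, b = 0.4: 0.64 / 0.80 × 1.022 = 0.82
- b = 0: 1.02 (with N = 40, 1 + 1/35 = 1.03)

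Simulation gives about 0.80 to 0.99 for slopes of 0.2 to 0.4, and 1.02 to 1.04 when expectancy has no effect.

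**7. Compared with the conditional use of baseline VAS.** Taking equal variances at baseline and week 6, ANCOVA on baseline VAS has variance (1 − rho²) / (2(1 − rho)) = (1 + rho)/2 relative to the t test on change. At rho = 0.5 that is 0.75, a 25% reduction. Over rho = 0.3 to 0.8 the reduction runs from 35% to 10%. In most of the assumed range this exceeds what expectancy adds.

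**The case against.** The strongest reply is that leaving out an optional covariate is a design preference. A two-group comparison without prognostic covariates is valid under randomisation, nothing in the article promises adjustment for expectancy, and this is a 50-patient pilot whose authors already name the small sample as a limitation. A further covariate could also be set in an analysis plan that is not shown. Most of this stands, and it is why the point is an improvement and not an error. It does not dispose of the point, because the article states its primary model, covariate included, and expectancy is not in it.

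A reader might infer more in four ways, none of which the document supports.
- **That expectancy is merely summarised.** It is also tested for homogeneity and may enter subgroup analyses.
- **That the result is biased, or that a large imbalance is likely.** Chance imbalance is not bias, the overall error stays near 5%, and an imbalance above 0.5 SD arises in about 8 to 11% of trials.
- **That the shift could reach 30% of the 15 mm MCID.** This needs a 2-SD imbalance together with the steepest assumed slope (2 × 0.283 × 0.4 × 20 = 4.5 mm). The 15 mm is also a responder threshold for a patient, not a design difference between arms.
- **That the screening VAS is an equally clear omission.** It appears only as an entry rule, "indicating pain of more than 40 mm on the visual analog scale (VAS) at the time of screening". It is truncated by that rule, and its interval from baseline is not stated in the text. The variance ratio from adding it was only 0.92 to 0.99 under the assumptions tried.

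**Conclusion.** The point holds as a modest, inexpensive improvement. Expectancy is collected before allocation and the primary comparison never adjusts for it. The planned test is valid and unbiased overall. What is forgone is some precision, and protection in the trials where the arms differ on expectancy by chance.

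Under the assumed SD and slopes, a 1-SD imbalance moves the estimate by about 1 to 2 mm, well inside the standard error of about 5.7 mm. Adjustment lowers the variance by about 1 to 20% relative to ANCOVA on baseline VAS. All of this depends on expectancy being prognostic, which the article neither shows nor quantifies. If its correlation with the outcome is near 0.1, adding it costs slightly more than it gains at 20 per arm (variance ratio 1.02).

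**What to change.** In the paragraph on the primary outcome under Statistical analysis, prespecify one ANCOVA of week-6 VAS (or of change) with group, baseline VAS and the pre-randomisation expectancy score, fitted whatever the observed balance. It replaces the rule that brings in baseline VAS only after a significant baseline difference; expectancy cannot sensibly be added while that rule stands. Report the same model without expectancy as a sensitivity analysis. The screening VAS can be left out or made optional.

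The cost is one sentence of wording and no new data. Beyond baseline VAS, expectancy uses one degree of freedom and adds about 2 to 4% to the variance if it turns out not to be prognostic.

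### Baseline adjustment of the primary VAS analysis depends on a baseline significance test; about 95% of trials would therefore use the less precise change-score t test instead of ANCOVA

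*Protocol article*

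**What the plan says.** All of this stands under Statistical methods in the protocol article.

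- **Primary comparison (Statistical analysis):** "The primary outcome, the mean changes from baseline to week 6 in the VAS scores, will be compared between the two groups", by t test or ANCOVA.
- **Selector (same paragraph):** "If the baseline difference in the VAS score between the two groups is statistically significant, an ANCOVA will be performed". The model is then fitted "with the baseline VAS score as a covariate and the study group as a fixed factor". No other criterion for choosing is given, so a non-significant baseline difference leads to the t test.
- **Baseline tests:** depending on normality, "baseline assessments for homogeneity will be conducted using the Wilcoxon rank sum test" or the t test.
- **Level:** "The significance level will be set at *p* < 0.05". Neither sidedness nor a separate level for the baseline test is stated.
- **Secondary outcomes:** "The secondary efficacy outcomes will be evaluated using the Wilcoxon rank sum test" or the t test if continuous. Neither test takes a covariate.
- **Sample size:** "a total of 50 participants will be an acceptable sample size, considering 20 participants in each group with a 20% drop-out rate". No power, effect size or SD is given.

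Randomisation is stratified by gender only, so baseline VAS is not balanced by design. A repeated-measures ANOVA on the visit trend is planned in addition. The article gives no adjusted primary analysis that is free of the baseline test.

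**The concern.** In a properly randomised trial any baseline difference is due to chance, so a significance test of it cannot show whether adjustment is useful. Baseline VAS is worth adjusting for because it predicts week-6 VAS, and that holds whether or not the arms happen to differ. Using the test as a gate means that adjustment is almost never applied. At this sample size the gate also lets through imbalances of more than half an SD.

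What is at stake is the precision of the primary estimate and its conditional bias. The Objective section makes efficacy against sham the primary aim and wants data for a full-scale trial, so the estimate and its variance will be carried forward. The Discussion lists the small sample as a limitation, which makes avoidable loss of information harder to accept.

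**Working it through.** **Inputs from the article:** 20 evaluable per arm, 20% drop-out, 50 in total; level 0.05; equal allocation; the selection rule above.

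**Assumptions not in the article:** two-sided tests; baseline test also at 0.05; bivariate normal VAS with equal SDs at both visits; pre-post correlation ρ of 0.3, 0.5 and 0.7. For power, SD 20 mm and a true difference of 15 mm. The article uses 15 mm as a minimal important change within a patient, so here it is only illustrative.

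**1. The plan's own figure.** 20 / (1 − 0.20) = 25 per arm, 50 in total. This reproduces. The number analysed lies between 20 and 25 per arm.

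**2. How often ANCOVA is used.** Under randomisation the baseline null hypothesis is true, so the test is positive with probability 0.05 (simulated 4.9 to 5.1%). About 95% of trials go to the t test on change.

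**3. What the gate lets through.** Largest non-significant difference = t(0.975, 2n − 2) × √(2/n):

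- n = 20: 2.024 × 0.3162 = 0.640 SD
- n = 25: 2.011 × 0.2828 = 0.569 SD

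At 20 per arm this is 6.4, 9.6 or 12.8 mm if the baseline SD is 10, 15 or 20 mm.

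**4. Precision.** With slope β of week-6 VAS on baseline, Var(change) / Var(ANCOVA) = 1 + (1 − β)² × Var(baseline) / Var(residual). With equal SDs, β = ρ and this becomes 2(1 − ρ) / (1 − ρ²) = 2 / (1 + ρ). Estimating the slope costs ANCOVA a factor of 1 + 1/(2n − 4) = 1.028 at n = 20.

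| ρ | 2/(1 + ρ) | after division by 1.028 |
|---|---|---|
| 0.3 | 1.54 | 1.50 |
| 0.5 | 1.33 | 1.30 |
| 0.7 | 1.18 | 1.15 |

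At ρ = 0.9 the ratio after the penalty is 1.02.

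**5. Effect of the entry cut-off.** Inclusion requires VAS above 40 mm at screening. If the cut acts on the baseline value itself (assumed mean 55, SD 20), Var(baseline) shrinks to 0.556 of its untruncated value while slope and residual variance stay the same. The ratios before the penalty become 1.30, 1.19 and 1.10. The loss in step 4 may therefore be smaller in practice.

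**6. Power and type I error.** Simulation of 100,000 trials per scenario:

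| | ρ = 0.3 | ρ = 0.5 | ρ = 0.7 |
|---|---|---|---|
| Power, planned rule, 20 per arm | 50% | 64% | 85% |
| Power, ANCOVA always, 20 per arm | 67% | 75% | 89% |
| Power, planned rule, 25 per arm | 60% | 75% | 92% |
| Power, ANCOVA always, 25 per arm | 77% | 84% | 95% |
| Type I error of planned rule, overall, 20 per arm | 4.0% | 4.4% | 4.6% |
| – baseline p 0.05 to 0.30 (25% of trials) | 8.1% | 7.7% | 6.6% |
| – baseline p above 0.30 (70% of trials) | 2.5% | 3.1% | 3.9% |

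ANCOVA stays at about 5% in each slice. Repeat runs moved the overall figure within 4.0 to 4.7% and the middle slice up to 8.6%.

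**7. Conditional bias.** The change score is biased by −(1 − ρ) times the imbalance. In the roughly 15% of trials (20 per arm) with an imbalance above 0.4 SD that is still non-significant, the mean bias is −0.35, −0.25 and −0.15 SD at ρ = 0.3, 0.5 and 0.7. At SD 20 mm that is 7, 5 and 3 mm (for example 0.35 × 20). For ANCOVA it is about zero.

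**The case against.** The strongest defence is that the rule is valid as it stands. It is written down in advance, depends on baseline VAS only, and is applied by a statistician blinded to allocation. This is a pilot without a power claim, and every power figure above rests on assumed inputs. All of that stands, and it rules out several stronger readings.

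- **That the rule inflates false positives.** It does not overall. The excess when baseline p is 0.05 to 0.30 is offset where p is above 0.30, and the total is slightly below 5%.
- **That the choice of test remains open until outcomes are seen.** The selector uses no outcome data, so there is no outcome-driven choice between the two tests.
- **That imbalance is ignored.** The primary outcome is change from baseline, which subtracts baseline in full. The fault is over-correction when the slope is below 1.
- **That a change score always loses to ANCOVA, or is the least precise analysis possible.** If the slope is 1, the variance ratio is 1 and ANCOVA pays a small degrees-of-freedom cost. Against a t test on week-6 VAS alone, change is worse only if ρ is below 0.5 (equal SDs).
- **That the entry cut-off makes matters worse.** Step 5 shows that it can do the opposite. The cut is applied at screening and baseline is taken at visit 1, so the net effect is uncertain.

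For the secondary outcomes, the article does not say whether raw or change scores are compared, and a fuller plan may. It does name tests that cannot adjust for baseline.

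Pilot status does not remove the point, because the article sets a significance level, makes efficacy the primary objective and intends the estimate to inform a larger trial.

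**Conclusion.** The point holds as a matter of efficiency and conditional bias. It is not a failure of overall validity. The article fixes a rule under which about 95% of trials would analyse the primary outcome without baseline adjustment. That follows from randomisation and the 0.05 level alone.

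The size of the loss depends on quantities the article does not give. With equal SDs, 20 per arm and correlations of 0.3 to 0.7, the change-score variance is about 1.5 to 1.15 times that of ANCOVA, and less if the entry cut-off narrows the baseline spread. With SD 20 mm and a 15 mm difference, ANCOVA in every case gains about 17, 11 and 4 percentage points of power (67 − 50, 75 − 64, 89 − 85). The gain shrinks as the correlation rises and vanishes as the slope approaches 1.

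**What to change.** In Statistical analysis, replace the conditional rule with one primary analysis: ANCOVA of VAS at week 6, or of the change (the treatment estimate is the same), with treatment group as factor and baseline VAS as covariate, whatever a baseline comparison shows. Preferably include gender too, since it is the stratification factor. Stop using the baseline test as a selector and present baseline data descriptively. Analyse NDI, PPT, HADS and EQ-5D in the same way, each with its own baseline value as covariate. The unadjusted t test on change can stay as a labelled sensitivity analysis.

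The cost is a change of wording, dated before allocation is revealed. Baseline VAS is already collected, so no new data, visits or participants are needed.

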#### Randomization and blinding

An independent, blinded statistician will generate the random number table by using the stratified randomization method of SAS® Analytics Pro (SAS Institute, Inc., Cary, NC, USA). The gender (male vs. female) will be applied as a condition value for the stratification. The random number table will be kept by the independent statistician and concealed with a password not to be exposed.

At visit 1, after baseline assessments, participants will be randomized into the experimental (real TEA treatment) group or the control (sham TEA treatment) group. Although the practitioner cannot be blinded, both participants and outcome assessors will be blinded to the allocation throughout the study period.

The study volunteers who have experience with TEA treatment will be excluded to prevent allocation guessing through discomforts, such as stiffness and irritation, post TEA treatment. Both the TEA treatment and the sham TEA treatment will be conducted by an individual practitioner, and identical treatment procedures in the same treatment room environments will be used. Because the sham TEA device appears identical to the real TEA device except for the thread hanging outside the needle, before starting the TEA treatment, the participants while in a sitting position will be instructed to turn their back on the practitioner to prevent them from being able to note the existence, or not, of the thread in the TEA needle.

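### Randomisation is stratified by gender, but no stated between-group efficacy comparison adjusts for it; if gender predicts VAS change, the main test is mildly conservative

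*Protocol article*

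**What the plan says.** The Design section describes a "single-center, equally randomized, two-armed, parallel, stratified (gender), subject-assessor-blinded, sham-controlled pilot trial". The Randomization and blinding section confirms the factor: "The gender (male vs. female) will be applied as a condition value for the stratification". No other factor is named.

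The Statistical analysis section then names the between-group efficacy analyses:

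- **Primary outcome** (VAS change from baseline to week 6): a t test or an ANCOVA. The ANCOVA is used if baseline VAS differs significantly between the arms, and its terms are listed: "with the baseline VAS score as a covariate and the study group as a fixed factor".
- **Visit trends:** "a repeated-measures analysis of variance (ANOVA) will be used to further confirm the differences in the trends of the visit". No gender factor is named.
- **Secondary outcomes:** "The secondary efficacy outcomes will be evaluated using the Wilcoxon rank sum test or the *t* test for continuous variables", with Fisher's exact or chi-square tests for categorical variables.

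Gender appears twice more. It is one of the baseline characteristics to be summarised by group, and subgroup analyses by baseline characteristics are planned for primary and secondary outcomes.

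**The concern.** Balancing the arms on gender reduces the true variance of the treatment difference if gender is prognostic for the outcome. A t test that ignores gender does not see that reduction: it still counts the between-gender spread as residual noise. The reported standard error, interval and p value then describe a less precise trial than the one that was run.

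This is not a detail left to an unseen analysis plan. The article names the test, the covariate and the fixed factor, and the stratification factor is not among them.

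What is at stake is precision. The trial plans on 20 evaluable participants per arm, calls its own sample small, and exists to supply data for a full-scale trial. Unnecessarily wide intervals make that product less useful.

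**Working it through.** **The plan's own figure.** The Sample size section takes 20 per group with 20% drop-out: 20 / (1 − 0.20) = 25 per group, 50 in total. This reproduces exactly. The article states no SD, effect size, power or standard error, so there is no precision figure to reproduce.

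**Inputs.** From the article: two arms, 1:1, stratified by gender; 20 per arm evaluable or 25 per arm randomised; significance level 0.05. Assumed: two-sided testing; gender mix 50:50 or 70:30; exact gender balance between arms; and R², the share of outcome variance explained by gender, from 0 to 0.20. For the ANCOVA, read R² as the share that remains after baseline VAS.

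**Formulas.** With gender balanced between arms:

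- unadjusted SE / gender-adjusted SE ≈ 1 / √(1 − R²)
- true type I error of the unadjusted test ≈ 2 × [1 − Φ(1.96 / √(1 − R²))]

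For example, at R² = 0.10 the ratio is 1 / √0.90 = 1.054, the effective critical value is 1.96 × 1.054 = 2.066, and the two-sided tail area is 3.9%.

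**Simulation check.** 20,000 trials per scenario, t test against a linear model with group and gender. Ranges cover 20 or 25 per arm and both gender mixes.

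| R² | SE ratio, formula | SE ratio, simulated | Type I, formula | Type I, simulated (unadjusted) |
|---|---|---|---|---|
| 0 | 1.000 | 1.000 | 5.0% | 5.0–5.2% |
| 0.01 | 1.005 | 1.005 | 4.9% | 4.9–5.0% |
| 0.05 | 1.026 | 1.027–1.028 | 4.4% | 4.3–4.6% |
| 0.10 | 1.054 | 1.056–1.058 | 3.9% | 3.7–4.1% |
| 0.20 | 1.118 | 1.123–1.125 | 2.8% | 2.7–2.9% |

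The gender-adjusted model stays near 5% throughout (4.7–5.3%).

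**Power.** For an assumed effect giving about 79% power at R² = 0 (0.9 SD at 20 per arm, 0.8 SD at 25), unadjusted against adjusted power is 79% v 79% at R² = 0, 80% v 81% at 0.05, 80–81% v about 83% at 0.10, and 81–82% v 87–88% at 0.20. If gender is irrelevant, the extra term costs essentially nothing.

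**What these R² values mean.** The implied difference between men and women in within-gender SDs is √(R² / [p(1 − p)]) / √(1 − R²). With a 30:70 mix, p(1 − p) = 0.21, and R² of 0.01, 0.05, 0.10 and 0.20 corresponds to differences of about 0.2, 0.5, 0.7 and 1.1 SD in VAS change. The upper values are large.

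**If the strata are not balanced.** With simple randomisation inside each gender stratum (40 or 50 participants in total, R² of 0.05 to 0.20), the unadjusted t test has a type I error of 4.8–5.1%. The conservatism therefore depends on balance being achieved, for example by blocking within strata.

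**The case against.** The strongest case against is that the effect is conditional and probably small.

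- **Gender must predict change, not pain level.** A constant difference in pain between men and women cancels in a change score. Nothing in the article says that gender predicts change. This stands, and it is why the range includes zero.
- **Balance is assumed.** The article names stratified randomisation but gives no blocking details, which a condensed article may leave out. Without balance the standard error is not too large, although adjustment can still gain precision. This also stands.
- **It is a pilot without a power calculation.** No stated power or precision claim is undermined. True, and it limits the importance of the point.
- **Drop-out is a weak argument for adjustment.** The main analysis uses everyone assessed at least once after allocation, with last observation carried forward, so many drop-outs remain and up to 50 people may be analysed.

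Three stronger readings are tempting, and the article does not support them. A reader might infer that gender enters no planned analysis. Subgroup analyses by baseline characteristics are planned and gender is listed as one, although subgrouping does not adjust the main comparison. A reader might infer that stratifying was pointless. It was not: any balance achieved, and the lower true variance, remain, and only the reported standard error fails to show them. A reader might infer that the main test is invalid in the dangerous direction. The error is conservative, with no bias and no excess of false positives.

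None of this removes the mismatch between how participants are allocated and how the arms are compared.

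**Conclusion.** The point holds as a modest efficiency flaw. Gender is the stratification factor, and no stated between-group efficacy comparison adjusts for it. Given balanced strata, the standard error is between 0% (R² = 0) and about 12% (R² = 0.20) too large, and the true type I error runs from 5% down to about 2.8%. At R² = 0.05 the power loss is about one percentage point, at 0.10 about three and at 0.20 about six. These sizes rest on assumed R² values, since the article supplies none, and values near zero are as compatible with it as the larger ones. The case for acting is that the adjustment costs almost nothing even when gender turns out not to matter.

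**What to change.** In the Statistical analysis section, make the primary model a linear model for week-6 VAS with study group and gender as fixed factors and baseline VAS as a covariate. With baseline VAS in the model, analysing week-6 VAS or change gives the same treatment estimate. Add gender to the models for continuous secondary outcomes. Compare the responder proportions (≥15 mm, ≥30%, ≥50%) with a gender-stratified method such as Cochran-Mantel-Haenszel.

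The cost is one degree of freedom per model: with all 50 analysed, 46 residual degrees of freedom instead of 47 for an ANCOVA on group and baseline VAS. The edit is more than one phrase, because models replace the default t test and the unstratified secondary tests, but the added work is small and gender is already recorded.
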